## Abstract

**Methods and analysis::**

This multicenter, prospective, observational registry study included 1000 participants diagnosed with FC. This study will collaborate with 3 comprehensive hospitals and 15 community hospitals and recruit patients into the registry between July 2022 and July 2023. After enrollment, we will collect the individual characteristics of each patient, anthropometric data and general condition, bowel movement, patient assessment of constipation symptoms, patient assessment of constipation quality of life, TCM syndrome scale, and time to take the laxative product again after treatment. We will also record adverse events and economic indicators at each visit.

**Discussion::**

This is the first registry-based study to collect real-world data of participants diagnosed with FC receiving BDT treatment. The results of this registry may also reflect these characteristics and provide direct clinical evidence to verify the importance of syndrome differentiation and treatment for the use of TCM health care products.

## 1. Introduction

Chronic constipation is a common disorder with a reported prevalence ranging from 3% to 27% in the general population.^[1,2]^ Its prevalence increases with age^[3,4]^ and consequently is expected to increase over the next few years.^[5]^ Functional constipation (FC) is a common functional gastrointestinal disease and one of the most common outpatient diseases. It refers to a group of independent clinical symptoms caused by non-organic causes, such as decreased frequency of defecation, difficult defecation, dry stool, and incomplete defecation, with a course of at least 6 months. FC can be classified into 3 categories: functional defecatory disorders, normal transit constipation, and slow-transit constipation.^[6]^ Different pathophysiological mechanisms may lead to FC, including abnormalities in the intestinal nervous system and neurotransmitters, dysfunction of cajal interstitial cells, abnormality of aquaporin, influence of intestinal flora, abnormal smooth muscle function, anxiety, and depression. Chronic constipation affects patients’ quality of life and can cause serious cardiovascular and cerebrovascular diseases.

The main treatment for FC is medication, including volume laxatives, irritant laxatives, prokinetic agents, osmotic laxative.^[7]^ In addition, colon hydrotherapy and biofeedback therapy can significantly improve the symptoms of patients with constipation.^[8]^ Traditional Chinese medicine (TCM) products have many advantages in health care and reduce the occurrence of chronic diseases. They have the characteristics of multicomponent, multitarget, and multichannel actions.^[9]^ However, there is not enough research to investigate the effectiveness of TCM health food, which is already in the market for the treatment of FC, and there is a lack of research on the characteristics of syndrome differentiation and treatment of TCM health products.

Besunyen Detox Tea (BDT) is a health tea used to improve gastrointestinal function, moisten the intestines, and relieve constipation among people with constipation for more than 20 years in China. BDT is a healthy Chinese tea consisting of six herbs, including Beishashen (Latin name: Glehniae Radix), Juemingzi (Cassiae Semen), Fanxieye (Sennae Folium), and Fuling (Poria Cocos (Schw.) Wolf.), Shanyao (Rhizoma Dioscoreae), and Lvcha (Camellia sinensis). Anthraquinone glycosides, free anthraquinones, and other polyphenols are the main components responsible for the laxative effect of Chinese herbal medicine.^[10]^

To investigate the efficacy and safety of traditional medicine BDT for FC, we conducted an observational registry study in the gastrointestinal clinic of 3 comprehensive hospitals and 15 community hospitals. To further compare the effect of BDT between constipation patients with dryness-heat syndrome and non-dryness-heat syndrome to reflect the characteristics of syndrome differentiation and treatment of TCM health care products.

## 2. Participants and Methods

### 2.1. Study design

The aim of the proposed study was to conduct a multicenter, prospective, observational registry study with 1000 participants who were diagnosed with FC (Fig. 1). The diagnosis of FC was based on the Rome IV criteria. Participants who voluntarily signed a written informed consent form after receiving sufficient explanation of the benefits and risks of participating in the study will be evaluated for compliance with the inclusion and exclusion criteria through a screening process on their first visit. After screening, eligible participants were assigned to the registry. BDT will undergo for 2 weeks and there will be 2 weeks of follow-up after the treatment. Participants could stop taking the BDT if FC was relieved after continuous treatment for at least 7 days.

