**Figure 1. F1:**
[figure not shown]
Study flow chart. BDT = Besunyen Detox Tea, FC = functional constipation, PAC-QOL = Patient Assessment of Constipation Quality of Life questionnaire, PAC-SYM = Patient Assessment of Constipation Symptoms questionnaire, TCM = traditional Chinese medicine.

The efficacy and safety of BDT in patients with FC has been accurately recorded under real conditions. The natural grouping method was used in this study, and the participants were not divided into groups or queues in advance. They will be divided into a dryness-heat syndrome group and a non-dryness-heat syndrome group by filling out the TCM syndrome scale when entering the study. The laxative efficacy of the two groups will be analyzed from different perspectives.

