### 2.5. Exposure

The participants will receive treatment with BDT (Beijing Aote Shuer Health Care Product Development Co. Ltd, Lot Number: 01200703, Beijing, China) twice a day (1 hour after lunch and 1 hour after dinner). The specification of tea is 2.5g/bag, and it is brewed once with 150 to 250 mL of boiling water. Health food and drugs (including dietary fiber and probiotics) with laxative effects shall not be taken orally and externally 4 weeks before the trial and during the trail, which will affect the judgment of the results.

During the experiment, the diet, drinking water, exercise, and rest were basically the same as before. If the constipation is aggravated, it is recommended that the participant go to the hospital for physical examination and use other laxative drugs. In case of serious adverse reactions, the participant shall immediately stop taking this product and seek medical treatment in time. The trial unit will bear the treatment costs and corresponding compensation arising therefrom.

The compliance of the participants was monitored by the counting method of the test products. Compliance = (actual dose/expected dose) × 100%.

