### 2.6. Outcomes measures

Researchers determined that the following data will be collected to observe the efficacy and safety of the TCM BDT for FC. The detailed research schedule for this registry study is presented in Table 1.

**Table 1 T1:** Research schedule of the registry study.

	Enrollment baseline	Subsequent visits	End of treatment	Subsequent visits
		The 7th day		The 14th day after the end
Informed consent	√			
Eligibility screening	√			
Matters needing attention	√			
Demographic characteristics	√			
Physical examination form	√	√	√	√
Bowel movement dairy (everyday)	√	√	√	√
PAC-SYM	√	√	√	√
PAC-QOL	√	√	√	√
TCM Syndrome Scale*	√	√	√	√
Economic questionnaire			√	
AEs		√	√	√

Note: the time window is specified as 5 days.

AE = adverse events, PAC-QOL = Patient Assessment of Constipation Quality of Life questionnaire, PAC-SYM = Patient Assessment of Constipation Symptoms questionnaire, TCM = traditional Chinese medicine.

* Only for people with dryness-heat syndrome.

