### 2.9. Statistical analysis plan

All statistical analyses were conducted using two-tailed tests and the significance level was set at 5%. An analysis of covariance will be performed when it is necessary to control for underlying variables, such as demographic variables. The propensity score can effectively balance the distribution and composition of each characteristic variable between groups and evaluate the relationship or role between intervention measures and outcome variables. It is often used to control for confounding bias among non-randomized groups in observational studies. The generalized estimating equation has obvious advantages over other methods for evaluating propensity score values and is the most recommended algorithm among the current evaluation methods for propensity score values.^[13]^ The mean of other scoring data will be analyzed using the *t* test or the chi-square test. The incidence of AEs within the groups was also evaluated using the chi-squared test. For missing data, the last observation carried forward will be used through a case report form inspection to replace the missing value. All statistical analyses in this study were conducted using SPSS 20.0 (SPSS Inc., IBM Corp., Armonk, NY).

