## 3. Discussion

This paper describes the protocol of a multicenter, prospective, registry-based observational registry study to monitor the efficacy and safety of the TCM BDT for FC. BDT is a functional food for Chinese herbal tea bags, which has a laxative effect and has been commonly used among people with constipation for more than 20 years in China. In particular, the active ingredients of BDT, such as total anthraquinones, sennoside A, sennoside B, and rhein, are the main compounds of BDT in the treatment of constipation. Previous studies have demonstrated that anthraquinone, especially its dianthrone compounds, such as sennoside A and sennoside B, exert significant laxative effects in promoting gastrointestinal motility and relieving FC.^[14]^

There are a large number of TCM health foods in China, but the guiding principles for the use of TCM health foods are currently lacking. In order to maximize the effect of TCM health foods on the importance of the application of TCM syndrome differentiation to health products, we put the standard of syndrome differentiation into the design of this study. As we know, TCM has its own properties (such as hot or cold), and it is theoretically believed that BDT has a better effect on constipation patients with dryness-heat syndrome. We aimed to identify the most suitable syndrome or clinical manifestation of BDT in this study.

This study is the first registry-based study to collect real-world data of participants diagnosed with FC receiving BDT treatment in community hospitals. The results of this registry may demonstrate the acceptance of BDT in patients and evaluate the effectiveness and safety of BDT for FC. Second, the long-term effect of BDT on FC was evaluated by observing the time the participants used the laxative product within 2 weeks of the end of the trial. Furthermore, the laxative effect of BDT on people with different syndromes (dryness-heat syndrome and non-dryness-heat syndrome) was investigated. The factors that affect the efficacy of BDT are analyzed by multiple factors, such as the severity of constipation, age, sex, occupation, and medical history. Finally, we evaluate the economic value of BDT. This is the first study to evaluate the effectiveness of TCM health products that are already on the market for people with different syndromes. This study has great significance.

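### Adverse-event incidence is tested without regard to days on BDT, although relieved participants may stop from day 7, so a syndrome-group safety difference may partly reflect unequal exposure

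*Protocol article*

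**What the plan says.** Section 2.1 sets the course and the follow-up: "BDT will undergo for 2 weeks and there will be 2 weeks of follow-up after the treatment". It then lets relieved participants end sooner: "Participants could stop taking the BDT if FC was relieved after continuous treatment for at least 7 days". Stopping is optional, and seven days is a minimum.

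Under Figure 1 the same section defines the only groups in the study, formed from the TCM syndrome scale at entry: "They will be divided into a dryness-heat syndrome group and a non-dryness-heat syndrome group".

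Table 1 (section 2.6) records AEs on day 7, at the end of treatment, and on "The 14th day after the end", with a 5-day time window.

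Section 2.9 gives the AE analysis in one sentence: "The incidence of AEs within the groups was also evaluated using the chi-squared test". Tests are two-sided at the 5% level. The same section offers analysis of covariance for underlying variables such as demographics, and propensity scores for imbalance between groups.

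Section 2.5 counts the product used: "Compliance = (actual dose/expected dose) × 100". Section 3 gives the sponsor's expectation: "it is theoretically believed that BDT has a better effect on constipation patients with dryness-heat syndrome".

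**The concern.** Section 2.1 makes time on BDT a consequence of response, while section 2.9 tests a proportion of participants that ignores time on BDT. Someone who stops on day 7 has half the planned exposure in which to have an on-treatment AE.

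This matters when the syndrome groups are compared. If more participants in one group are relieved and stop, that group contributes fewer exposed days. Its AE proportion can then be lower although the risk per day is the same. The sponsor expects a better effect in dryness-heat syndrome, so unequal stopping is plausible under its own hypothesis.

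The adjustments named in section 2.9 deal with baseline differences. Days on BDT arise after baseline and follow from response, so those adjustments do not remove the problem.

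Safety is a stated aim alongside efficacy (sections 1 and 3). What is at stake is whether a difference in AE incidence can be read as a difference in tolerability.

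**Working it through.** The protocol states no AE rate, early-stop share or AE timing, so there is no safety figure of its own to reproduce.

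**From the documents**
- Planned exposure is 14 days and the minimum for a relieved participant is 7 days (section 2.1). The extreme exposure ratio is 7/14 = 0.50.
- The test is two-sided at 5% (section 2.9).
- The total is at least 1000 (section 2.8). Syndrome-group sizes are not given.

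**Assumed**
- The 14-day on-treatment AE risk is p14 = 10%, with the same daily hazard in both groups.
- A share f of each group stops at exactly day 7; the rest take all 14 days.
- Group sizes are 500 and 500.

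**Step 1: risk over 7 days.** With a constant hazard, p7 = 1 − (1 − p14)^(7/14) = 1 − 0.9^0.5 = 5.13%.

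**Step 2: group incidence** = f × p7 + (1 − f) × p14.

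| Share stopping at day 7 | Incidence, group A | Incidence, group B | Ratio |
|---|---|---|---|
| 60% vs 20% | 0.6 × 5.13 + 0.4 × 10 = 7.08% | 0.2 × 5.13 + 0.8 × 10 = 9.03% | 0.78 |
| 50% vs 40% | 0.5 × 5.13 + 0.5 × 10 = 7.57% | 0.4 × 5.13 + 0.6 × 10 = 8.05% | 0.94 |
| 40% vs 40% | 8.05% | 8.05% | 1.00 |
| 100% vs 0% (extreme) | 5.13% | 10% | 0.51 |

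**Step 3: effect on the test.** With no true difference in daily risk, the chance of a significant result favouring the earlier-stopping group is about 20% at 60% versus 20%, and about 5% at 50% versus 40%. These figures count one direction only, where a valid test would give 2.5%. With 60% versus 30% and a 14-day risk anywhere from 5% to 30%, the ratio is 0.83 to 0.84. The chance is then 9% to 33% (7% to 28% with groups of 300 and 700).

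**Step 4: when the AEs occur.** Let s be the share of the 14-day cumulative hazard that falls in days 1–7, so p7 = 1 − 0.9^s. At 60% versus 20%:
- s = 0.50 (constant hazard): ratio 0.78, as above.
- s = 0.75: p7 = 7.60%, incidences 8.56% and 9.52%, ratio 0.90.
- s = 1.00: both 10%, ratio 1.00.

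**Step 5: would a person-day rate cure it?** At 60% versus 20%, mean days on BDT are 14 − 7 × 0.6 = 9.8 and 14 − 7 × 0.2 = 12.6. With a constant hazard the rate ratio is 1.00. If all AEs fall in week 1, both groups have the same events over different days. The rate ratio is then 12.6/9.8 = 1.29 against the earlier-stopping group, and 14/7 = 2.00 in the extreme case. The rate therefore replaces one artefact with another unless the hazard is constant.

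**The case against.** A reader might infer that the better-responding group will look safer, and only because it was exposed less. The documents do not support that. The artefact needs both unequal early-stop shares and AEs after day 7, and neither is documented. Section 3 speaks, as theory, of a better effect and says nothing of speed. Half exposure is the extreme of an optional rule. At 50% versus 40% the distortion is small. All of this stands.

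A second objection is that no between-group safety test is clearly planned: section 2.9 says within the groups, and section 2.1 promises a comparison of laxative efficacy. This stands in part. The wording is ambiguous, but a chi-squared test on incidence most naturally compares groups, and no others are defined.

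Third, the registry observes BDT under real conditions, with stopping on relief as part of use. The proportion with an AE is then a valid risk for BDT as used, and the protocol never claims it as the risk of a full 14-day course. This stands. The fault would lie in reading a group difference as one of tolerability.

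Fourth, the text does not say that on-treatment and later AEs are pooled. Nor does it say whether the last visit is timed from the last dose or from day 14, so total observation for early stoppers (about 21 days or about 28) is uncertain. This also stands.

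Finally, exposure-adjusted tables are ordinary analysis-plan content, and that plan is not shown. This is fair as to omissions, but the chi-squared test on incidence is a stated method, and the point concerns what that method can show. Exposure is largely recoverable from the product count, which makes the remedy cheap but does not make the stated test sound.

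**Conclusion.** The concern holds in a conditional form. Exposure depends on response by design, the stated AE test ignores it, and the planned baseline adjustments cannot correct it. A syndrome-group difference in AE incidence may therefore be due in part to time on BDT.

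Across the partial-stopping cases shown, the ratio produced by exposure alone runs from 0.78 to 1.00; complete separation of the groups gives 0.51. These figures rest on assumed AE risks, stopping shares and group sizes, with all early stopping at day 7. They shrink as AEs concentrate in the first week. The documents establish neither that the artefact will occur nor which group it would favour. A change is worth making, at medium confidence.

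**What to change.** Leave the stop rule as it is and change the safety analysis:

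1. Keep the per-participant AE incidence, labelled as the risk of BDT as used and not of a full 14-day course.
2. Report days on BDT by syndrome group, from a last-dose date or, failing that, the product count.
3. Split AEs into those starting on BDT and those starting after the last dose. Use onset dates, because the 5-day visit window makes the day-7 visit an imprecise boundary.
4. Base the syndrome-group safety contrast on AE incidence in days 1–7, the window common to early and later stoppers, and on cumulative incidence by day on treatment. Beyond day 7, treat the curve as descriptive, since those still on BDT will include fewer of the relieved.
5. Give AEs per person-day on BDT as a supporting figure only, stating that it assumes a constant hazard and would make early stoppers look worse if AEs cluster in week 1.
6. Reword the section 2.9 sentence to say whether the chi-squared test compares the syndrome groups, and over which window.

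The cost is at most one date field and a few more safety tables. The full-course figure may prove less favourable than the simple proportion.

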**Figure 1. F1:**
[figure not shown]
Study flow chart. BDT = Besunyen Detox Tea, FC = functional constipation, PAC-QOL = Patient Assessment of Constipation Quality of Life questionnaire, PAC-SYM = Patient Assessment of Constipation Symptoms questionnaire, TCM = traditional Chinese medicine.

The efficacy and safety of BDT in patients with FC has been accurately recorded under real conditions. The natural grouping method was used in this study, and the participants were not divided into groups or queues in advance. They will be divided into a dryness-heat syndrome group and a non-dryness-heat syndrome group by filling out the TCM syndrome scale when entering the study. The laxative efficacy of the two groups will be analyzed from different perspectives.

### 2.2. Trial registration

This study was registered with the Chinese Clinical Trial Registry (http://www.chictr.org.cn). (Registration No.: ChiCTR2200061535), and the registration was on June 28, 2022, version 3.0. URL of trial registry record: http://www.chictr.org.cn/showproj.aspx?proj=172303.

#### 2.3.2. Exclusion criteria.

Those with unclear complaints, those who were too weak to carry out the study, and those who could not eat orally; Constipation symptoms caused by surgery within 30 days; Acute gastrointestinal disease occurred within 30 days of admission; Menstruation, pregnancy preparation, pregnancy, and lactation; Patients with serious systemic diseases of the cardiovascular, liver, kidney, and hematopoietic systems; Constipation with abdominal pain (irritable bowel syndrome); Recent defecation difficulties caused by severe organic diseases (colon cancer, severe enteritis, intestinal obstruction, inflammatory bowel disease, etc); History of drug and food allergy or contraindications to the study product; Mental disorders and cognitive dysfunctions; There are other accompanying diseases under treatment; Health food and drugs (including dietary fiber and probiotics) with laxative effects will be taken orally and externally 4 weeks before the trial, which will affect the judgment of the results.

### 2.4. Recruitment

Participants will be recruited from 3 comprehensive hospitals and 15 primary medical institutions across China. We will also advertise through websites and post recruitment posters on the walls of the entrance of each clinic to encourage voluntary participation in this study. If the participants met the inclusion criteria in this study, the researcher will fully explain the aim of this study and details of the procedures, including research usage, confidentiality, and provision of data to third parties for analysis, and will obtain informed consent from the potential participants. Simultaneously, professional clinicians will be arranged to observe the status of the participants and provide medical assistance.

### 2.5. Exposure

The participants will receive treatment with BDT (Beijing Aote Shuer Health Care Product Development Co. Ltd, Lot Number: 01200703, Beijing, China) twice a day (1 hour after lunch and 1 hour after dinner). The specification of tea is 2.5g/bag, and it is brewed once with 150 to 250 mL of boiling water. Health food and drugs (including dietary fiber and probiotics) with laxative effects shall not be taken orally and externally 4 weeks before the trial and during the trail, which will affect the judgment of the results.

During the experiment, the diet, drinking water, exercise, and rest were basically the same as before. If the constipation is aggravated, it is recommended that the participant go to the hospital for physical examination and use other laxative drugs. In case of serious adverse reactions, the participant shall immediately stop taking this product and seek medical treatment in time. The trial unit will bear the treatment costs and corresponding compensation arising therefrom.

The compliance of the participants was monitored by the counting method of the test products. Compliance = (actual dose/expected dose) × 100%.

